### Sample Size

A total of 344 participants will be included in the RCT. This sample size calculation was based on the results of prior trials exploring the effectiveness of comparable digital interventions which report effect sizes (Cohen *d*) ranging from 0.48 to 0.56 [17,18,59]. In addition, a similar effect size was used to determine the sample size for a similar RCT observing the effectiveness of a WHO-developed digital health intervention, based on a conservative, yet clinically significant effect size of 0.5 [60]. Assuming an effect size of 0.5 at a 3-month follow-up (power=90%; α=0.05, 2-sided), the trial would require 172 participants (STARS=86 and EUC=86). Given the high attrition rates reported in digital intervention studies, a conservative attrition rate of 50% was assumed. This attrition rate was informed by the results of the feasibility RCT and comparisons with protocols for similarly designed studies.

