### Statistical Analysis

To measure baseline differences between the 2 treatment arms, 2-tailed *t* tests will be conducted for continuous variables and chi-square tests for categorical data. To determine the effectiveness of the STARS intervention, intention-to-treat analysis will be conducted to compare the mean difference between STARS and EUC at baseline, post intervention, and 3-month follow-up. Differential change over time between treatment arms will be assessed using linear mixed models that accommodate missing data at subsequent assessments and provide differential slopes of trajectories between conditions. Hierarchical linear models study treatment effects because this allows the number of observations to vary between participants and handles missing data by using maximum likelihood estimation methods. Missing data will be assumed to be random if participants retained and not retained at 3 months do not differ on baseline characteristics. Fixed (intervention and time of assessment) effects and their interactions will be entered in unstructured models to yield indices of the relative effects of the treatments; time of assessment included baseline, post treatment, and 3-month follow-up. Analyses will focus on the primary outcome and secondary measures, with the main outcome time point being the 3-month follow-up relative to baseline. A subsequent per protocol completers analysis will be conducted, only including those who completed the 3-month follow-up, in order to assess the robustness of the primary analysis.

In addition to these analyses, the role of potential moderators and mediators, such as agency, on outcomes will be explored independently using the PROCESS macro. Two-tailed tests with a significance level of *P*<.05 will be reported for all analyses.

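### The primary contrast estimates a separate baseline mean in each arm; a common baseline mean would make it more precise at no cost

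*Protocol article*

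**What the plan says.** The Statistical Analysis section of the protocol article enters arm, time of assessment and their interactions as fixed effects in a linear mixed model fitted by maximum likelihood. Baseline is one of the response times: "time of assessment included baseline, post treatment, and 3-month follow-up". The main result is taken "with the main outcome time point being the 3-month follow-up relative to baseline". The section mentions neither a baseline covariate nor a common baseline mean. It also plans significance tests of baseline differences and lists baseline among the times at which the arms are compared.

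Under Randomization and Blinding, allocation follows completion of the baseline assessment.

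The Sample Size section reads: "Assuming an effect size of 0.5 at a 3-month follow-up (power=90%; α=0.05, 2-sided), the trial would require 172 participants", that is 86 per arm. It adds that "a conservative attrition rate of 50% was assumed", which gives 344 randomized. It states no correlation between baseline and follow-up and does not say which standard deviation scales the effect size.

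**The concern.** A model with an arm main effect and baseline as a response gives each arm its own baseline mean. The arm-by-time term at 3 months is then a difference in changes, and it carries the sampling error of two estimated baseline means. Because baseline is measured before allocation, any difference between those means is chance. Estimating it adds variance to the primary contrast and brings nothing in return.

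At stake is precision at the time point where data will be scarcest, since half of the participants may be missing at 3 months. If the assumed effect is in 3-month score units, the planned contrast could also have less than 90% power when baseline predicts the 3-month score only weakly.

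**Working it through.** **Inputs from the article (Sample Size; Randomization and Blinding).** d = 0.5; two-sided alpha 0.05; power 90%; 86 per arm evaluable; 50% attrition; 344 randomized 1:1, so n = 172 per arm randomized and m = 86 per arm observed at 3 months.

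**Assumptions.** Equal SDs at all times (set to 1); d in 3-month SD units; correlation ρ between baseline and 3 months, not given in the article and so varied from 0.2 to 0.7.

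**Step 1: the article's own figure.** A two-sample t-test at d = 0.5 and 90% power needs 85.03 per arm, rounded up to 86. Then 172/(1 − 0.5) = 344. Both figures reproduce. With 86 per arm, SE = √(2/86) = 0.1525 and power = Φ(0.5/0.1525 − 1.96) = 90.6% (90.3% with the t distribution).

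**Step 2: variance of the planned contrast.** In each arm, maximum likelihood uses all n baselines and the m follow-ups. The variance of the estimated change is (1 − ρ²)/m + (1 − ρ)²/n. For the difference between arms:

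Var(planned) = 2[(1 − ρ²)/m + (1 − ρ)²/n]

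**Step 3: variance with a common baseline mean, or baseline as covariate.**

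Var(common) = 2(1 − ρ²)/m

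The second term of the planned variance is the price of the two free baseline means. Relative to 2/86, the planned variance is (1 − ρ²) + (1 − ρ)²/2 and the common-mean variance is 1 − ρ². A generalized-least-squares information matrix for three visits gave the same results.

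**Step 4: results.** Power = Φ(0.5/√Var − 1.96). Example at ρ = 0.2: planned relative variance 0.96 + 0.32 = 1.28, SE = 0.1525 × √1.28 = 0.1725, power 82.6%; common mean 0.96, SE 0.1494, power 91.7%; variance reduction 1 − 0.96/1.28 = 25%.

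| ρ | Planned variance | Common-mean variance | Reduction | Planned power | Common-mean power |
|---|---|---|---|---|---|
| 0.2 | 1.280 | 0.960 | 25% | 82.6% | 91.7% |
| 0.3 | 1.155 | 0.910 | 21% | 86.2% | 93.0% |
| 0.4 | 1.020 | 0.840 | 18% | 90.1% | 94.7% |
| 0.5 | 0.875 | 0.750 | 14% | 93.9% | 96.6% |
| 0.6 | 0.720 | 0.640 | 11% | 97.2% | 98.4% |
| 0.7 | 0.555 | 0.510 | 8% | 99.3% | 99.6% |

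**Step 5: where the planned contrast crosses 90%.** At 50% attrition it does so at ρ of about 0.40. It matches a plain comparison of 3-month scores (relative variance 1) at ρ = √2 − 1 = 0.414; below that, ignoring baseline would be more precise.

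**Step 6: sensitivity to attrition.** At ρ = 0.3, 101 per arm followed gives 2(0.91/101 + 0.49/172) = 0.0237 and power 90.1%; that is attrition of 71/172 = 41%. At ρ = 0.2, 118 per arm gives 90.1%; that is attrition of 54/172 = 31%.

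**Step 7: sensitivity to 8-week data.** Suppose half of those missing at 3 months still give the 8-week score, the baseline-to-8-week correlation is ρ, and the 8-week-to-3-month correlation is ρ + 0.15. Power is then 83.6% planned against 92.6% with a common mean at ρ = 0.2, 87.6% against 94.2% at 0.3, and 95.5% against 97.8% at 0.5. The pattern is the same.

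**The case against.** The strongest reply is that nothing here is an error. Between randomized arms, a difference in changes is unbiased and keeps its type I error, so the proposal only optimises an acceptable method. That stands, and the point is made as an efficiency improvement. The further argument, that a condensed article leaves such detail to the analysis plan, carries less weight: the fixed effects, the status of baseline and the contrast are all stated.

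Three stronger readings are tempting, and the article does not support them.

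- A reader might infer that the trial is underpowered. That needs a correlation under about 0.40 together with attrition near 50%, a rate the article itself calls conservative. The correlation is not given, and nothing shows that it is so low.
- A reader might infer that the sample size was computed for a different estimator. The article says "Assuming an effect size of 0.5 at a 3-month follow-up" without naming the standardiser. If 0.5 is in units of the planned contrast, the 90% applies to it directly, and 86 per arm follows either way.
- A reader might infer that baseline is thrown away. Above a correlation of about 0.41 the planned model beats a plain 3-month comparison (93.9% against 90.6% at 0.5). Baseline helps there, only less than it could.

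A fair caution about the covariate form is that participants with neither follow-up leave the response data, while the article commits to intention-to-treat. They add no information on the 3-month arm difference in either form, but keeping all randomized participants in one model fits that commitment better.

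**Conclusion.** The point holds as an efficiency improvement, not as a demonstrated power error or bias. The variance reduction is 25% to 8% over correlations of 0.2 to 0.7 under equal SDs and 50% attrition, and some gain exists at every correlation below 1. The power figures also assume that d = 0.5 is in 3-month SD units. Under these assumptions a common baseline mean never gives less than the 90.6% of the plain 3-month comparison, whereas the planned contrast does so below a correlation of about 0.41.

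K10, a secondary outcome, deserves a separate note. The schedule in Table 1 has it at screening and at the two follow-ups but not at the baseline visit, so its only pre-randomization value is the eligibility score, cut off at 20. That value is better used as a covariate than as a normally distributed response. No bias in the arm comparison is shown.

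**What to change.** Keep the mixed model on all randomized participants but constrain the arms to a common baseline mean: time, arm-by-post-treatment and arm-by-3-month terms, with no arm effect at baseline. Equivalently for the arm difference, model the two follow-ups with baseline score and baseline-by-time as covariates. Report the arm difference at 3 months as the primary effect. For K10 use the covariate form, with the screening score as the covariate.

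The cost is a change of wording in the analysis section. Sample size and data collection stay as they are. The Results section says that no data had been analysed when the article was written, so at that stage the change could be specified without knowledge of results.

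### The completers analysis named as the robustness check is a complete-case analysis, not per protocol, and its agreement with the mixed model would not show robustness to dropout

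*Protocol article*

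**What the plan says.** The Statistical Analysis section of the protocol article states that an "intention-to-treat analysis will be conducted to compare the mean difference between STARS and EUC", using linear mixed models. It says that this approach "handles missing data by using maximum likelihood estimation methods", with "the main outcome time point being the 3-month follow-up relative to baseline". On the nature of the missingness it says: "Missing data will be assumed to be random if participants retained and not retained at 3 months do not differ on baseline characteristics".

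It then adds one further analysis, labelled per protocol, and gives its set and purpose: this "completers analysis will be conducted, only including those who completed the 3-month follow-up, in order to assess the robustness of the primary analysis".

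The Sample Size section needs 86 participants per arm for an effect size of 0.5 with 90% power. On loss to follow-up it says that "a conservative attrition rate of 50% was assumed", which gives the total of 344.

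The Interventions section describes STARS as 10 chatbot sessions plus 5 weekly e-helper calls. Neither appears in the definition of the per protocol set.

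**The concern.** Two things are fixed badly in the same sentence.

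- **The label.** A per protocol set is normally defined by receipt of the assigned treatment. Here, a STARS participant who opened no session but answered at 3 months is in, and one who finished all 10 sessions but did not answer is out. A reader of the results could take the estimate as the effect in adherent participants, which it is not.
- **The purpose.** A robustness analysis should relax or vary the assumption that the primary analysis depends on. The mixed model relies on data being missing at random (MAR) given the observed scores. Restricting to 3-month responders throws away the baseline and post-intervention scores of those lost. It is therefore valid only under a stricter condition, close to missing completely at random (MCAR). The check tightens the assumption it is meant to probe.

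At stake is how the trial's conclusion is defended. If half of the 3-month scores are missing, as planned for, a statement that the completers analysis confirmed the primary result would be offered as support for robustness that it cannot give.

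**Working it through.** **1. The plan's own figure.** Effect size 0.5, two-sided 5% level, 90% power: the t-test solution is 85.03 per arm, rounded up to 86, so 172 in total. Inflating for 50% attrition: 172 / (1 − 0.5) = 344. The sample size reproduces and is not in question. The planning case is 86 observed and 86 missing per arm at 3 months.

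**2. How the two analyses behave under different dropout.** Inputs from the protocol: three assessments, 1:1 allocation, 50% retained at 3 months, true effect −0.50 SD (lower scores are better). Assumed, not in the protocol: SD 1; correlations 0.5 (baseline with post-intervention), 0.5 (baseline with 3 months) and 0.6 (post-intervention with 3 months); the same effect at both later assessments; logistic dropout centred so that each arm retains 50%; post-intervention score observed for all unless stated. The sample was 2 million, so that bias rather than chance is seen. The mixed-model estimate was obtained by regressing the 3-month score on arm and earlier scores among responders and averaging the predictions over all randomised. The completer estimate is the difference in mean change among responders.

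| Dropout mechanism | Mixed model | Completers |
|---|---|---|
| Completely at random | −0.50 | −0.50 |
| STARS only, on post-intervention score, log-odds 1 per SD | −0.50 | −0.54 |
| STARS only, on unseen 3-month score, log-odds 0.5 per SD | −0.64 | −0.62 |
| STARS only, on unseen 3-month score, log-odds 1 per SD | −0.75 to −0.76 | −0.70 to −0.71 |
| As above, dropouts also lack the post-intervention score | −0.82 | −0.70 |
| Both arms, on unseen 3-month score, log-odds 1 per SD | −0.50 | −0.50 |

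In the second row the primary model is right and the check is off. In rows three and four both are wrong, in the same direction, and they differ by only 0.02 to about 0.05 SD. In the first and last rows both are right and they agree. Agreement therefore occurs both when the primary result is sound and when it is not.

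**3. What an analysis that varies the assumption would show.** Suppose that the estimate under MAR is a benefit of 0.5 SD and that half of STARS is missing. If the missing STARS participants are worse than MAR predicts by δ SD, the benefit becomes 0.5 − 0.5δ.

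- Unadjusted SE with 86 observed per arm: √(2/86) = 0.1525.
- Lower 95% limit: 0.5 − 1.96 × 0.1525 = 0.201.
- Tipping point, SE held fixed: δ = 0.201 / 0.5 = 0.40 SD.
- With baseline adjustment at an assumed r = 0.5: SE = 0.1525 × √(1 − 0.25) = 0.132; lower limit 0.241; δ = 0.48 SD.
- With an assumed r = 0.7: SE = 0.109; δ = 0.57 SD.
- If missing STARS participants did no better than EUC: 0.5 × 0.5 + 0.5 × 0 = 0.25 SD.

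With the same δ in both arms and equal retention, the shifts cancel and the effect stays at 0.5.

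**The case against.** The strongest reply has four parts.

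- **This is a condensed article and no SAP is shown.** Delta-adjusted or reference-based analyses are typical SAP content, and the article does not say that nothing else will be done. This stands as a limit. A reader might infer that the trial has no analysis of informative dropout at all; the document does not support that. The point rests on what the article does fix, namely the completer set as the robustness check and its label.
- **The bias needs dropout that differs by arm.** This also stands. With the same outcome-related dropout in both arms, both estimates are unbiased, and the protocol gives no retention by arm. A differential mechanism is plausible, since participants know their allocation and STARS has weekly calls while EUC is a website, but it is not established.
- **The two analyses can diverge.** They do when those lost also lack the post-intervention score (−0.82 against −0.70). A reader might go further and infer that the analyses agree precisely when both are biased. That is false, because they also agree, correctly, under MCAR. The sound statement is that agreement does not discriminate.
- **The label does little harm**, because the same sentence says who is included. This is partly right: correcting it is a change of wording. But the label tends to be carried into results tables without its definition.

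**Conclusion.** The point holds. The named robustness analysis is a complete-case analysis wrongly called per protocol. It needs a stricter assumption than the primary model, so agreement between the two would not show that the primary result is robust to dropout.

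The size is illustrative. With outcome-related dropout in STARS alone (log-odds 0.5 to 1 per SD) and the assumed correlations, both estimates overstate a true 0.50 SD effect. The mixed model does so by about 0.14 to 0.26 SD and the completers by about 0.12 to 0.21 SD. The amounts depend on the assumed slopes and correlations. The tipping point of about 0.40 SD assumes an estimate of exactly 0.5, half of STARS missing, an unadjusted SE and a shift in STARS only. The 50% attrition is the plan's own figure, which it calls conservative, so actual loss may be smaller.

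None of this shows that the primary mixed model is invalid or that the trial's result will be biased, and the sample size is unaffected. The change should be made, but it concerns the safeguard rather than the primary analysis.

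**What to change.** - For the robustness analysis, use all 344 randomised and vary the MAR assumption: delta-adjusted multiple imputation of missing 3-month HSCL-25 scores over a range stated in advance (for example 0 to 0.6 SD). Apply the shift to STARS alone and to both arms, allowing different values by arm because equal shifts largely cancel.
- Report the tipping point at which the conclusion changes. Reference-based imputation, with missing STARS scores modelled on EUC, is an option.
- Keep the completer result as descriptive and drop the words per protocol.
- If an adherence-based estimate is wanted, define it by sessions completed, since completion dates are already stored in OpenDialog, and adjust for baseline predictors of adherence.

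The cost is some extra programming, more analyses to report and a possibly less favourable robustness statement. No new data are needed. The article reports 228 randomised by 15 November 2023 and no analysis to date, so at that point the change could still be specified before results were known.

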### Data Management, Trial Monitoring, and AE Reporting

All assessment data will be collected electronically in Qualtrics. Participants will receive personalized Qualtrics links for their baseline, post-, and 3-month follow-up assessments so that assessments can be linked to each other. Only the research team will have access to the data in Qualtrics. Deidentified data stored from the STARS intervention (eg, PHQ-2 scores, free-text responses, session completion date) are available to e-helpers and the research team through the OpenDialog website. Data collected online will be held securely and separately from study data, according to the relevant data protection laws. Data will be deidentified and stored confidentially at the University of New South Wales after transferring to an SPSS database.

An identifying key list (a list connecting names to numbers) will be kept by the project manager at IFH. All downloaded electronic data will be pseudonymized and stored on password-protected computers. Hardcopy files of the study, such as supervision notes, will be stored in locked cabinets at IFH. No identifiable data will be used in publications or presentations. Trial monitoring will be done by WHO staff on a biweekly basis to ensure the accuracy of data storage and output.

AEs or serious AEs (SAEs) refer to any undesirable experience of a participant during the trial, whether or not considered related to the trial procedures or to the STARS or EUC interventions. All AEs or SAEs reported spontaneously by participants or observed by the research team or e-helpers will be reported to the IFH clinical supervisor for immediate action and resolution where required. All SAEs will be reported to the local ERC within 24 hours of being informed about the event, and a summary of AEs will be reported to the local ERC every three months. The local ERC will review any SAEs as soon as possible and the summary of AEs during their regular meetings. They will determine any appropriate action with respect to ongoing study conduct. Additionally, all SAEs will be reported to the WHO ERC. As STARS is nonpharmacological and there exists a broad evidence base for the safe use of e-interventions and therefore a low risk for adverse effects, no Data Monitoring Safety Board will be installed for this study. Adverse events will be monitored and reported to the local ethics committee.

Any modifications to the protocol that may impact the conduct of the study, the potential benefit of the participant, or may affect participant safety will require a formal amendment to the protocol. Such amendment will be reviewed and approved by the local ethics committee of the University of Jordan and by the WHO ERC prior to implementation. Administrative changes are minor corrections and/or clarifications that have no effect on the way the study is to be conducted. These administrative changes will be documented in a memorandum and communicated to the WHO ERC.

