The training and materials for the guided component of the chatbot intervention are based on a guided self-help approach developed by WHO and used in several studies [17,18,46]. It consists of 5 weekly telephone calls by trained, nonspecialist e-helpers. The support calls last approximately 15 minutes each to provide participants with support and guidance to implement the STARS intervention techniques and to use the STARS intervention chatbot. E-helper support is strongly protocolized and outlined session-by-session for each support phone call in an e-helper manual. E-helpers are trained on the STARS intervention and research protocols during a 5-day training delivered by IFH. The training includes knowledge about psychological distress and other mental health problems, communication skills, providing support, responding to distress, and procedures for adverse events (AEs) including referral procedures. E-helpers can monitor their participants’ progress through the OpenDialog system and can view some of the participants’ responses. These are limited to specific parts that are relevant for the e-helper, such as responses to the mood check, the goal a participant selected, and free-text fields. Free-text responses will be monitored on a daily basis for any indications that the participant is unsafe (eg, in case a participant expresses suicidal ideation in a free-text field or suggests a harmful goal to work on in the intervention). E-helpers will be supervised on a weekly basis by a clinical supervisor based at IFH, with additional support to the project team from WHO. Clinical group supervision will ensure fidelity of the e-helper support calls, discussion of challenging situations when providing telephone support, and e-helper self-care. The clinical supervisor will also listen to 5% of e-helper support calls to provide feedback on the delivery of the support calls.

To evaluate treatment fidelity, a random sample (5%) of e-helper support calls will be audio recorded. Participants will be asked for verbal consent prior to recording. Recordings will be evaluated according to a treatment fidelity checklist. This information has also been added to the consent form.

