#### Enhanced Usual Care

The EUC intervention will include basic psychoeducation regarding depression and anxiety, as well as resources on available evidence-based care available in Jordan. This will be delivered through a website where participants register to gain access. The information provided to those in EUC will also be provided during the psychoeducation session to those enrolled in the STARS intervention. Available resources will include a list of organizations that offer evidence-based mental health and psychosocial support in Jordan—as this study is taking place at a national level, a list has been created of the resources available across the country so that those in need can access services close to their physical location.

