#### Other Measures

To capture any mental health services that participants received prior to or during the study period, 2 items will be included in postassessments to capture information on the use of psychological or counseling services and medications (each item answered with yes or no).

Those randomized into the STARS intervention will complete the Patient Health Questionnaire, 2-item version (PHQ-2) [58] during every other session. The PHQ-2 has been shown to allow for the detection and monitoring of depression over time and will allow the research team to identify potential worsening of symptoms in participants during the intervention phase [58]. The measure inquiries about symptoms of depression over the past 2 weeks, with items scored on a 4-point Likert scale ranging from 0=not at all to 3=nearly every day, with scores ranging from 0 to 6.

Finally, user satisfaction of the STARS intervention will be assessed through a version of the Client Satisfaction Questionnaire, a scale intended to measure client satisfaction with health services, adapted specifically for web-based health interventions [44]. The questionnaire includes 8 items scored on a 4-point Likert scale ranging from 1=does not apply to me to 4=does totally apply to me. The assessment will be offered to participants during the post-intervention assessment as an optional additional questionnaire.

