### Safety Considerations

The therapeutic techniques included across the 10 lessons are evidence-based, and therefore, it is unlikely that participants in the intervention will experience an increase in psychological distress. The PHQ-2 will be administered in the STARS intervention once a week (every other lesson) and will be monitored by e-helpers to track participants’ levels of distress during the intervention phase of the trial.

The development of the STARS intervention was intended to minimize the risk of potential adverse events. Of particular focus was to minimize the loss of privacy or confidentiality of intervention participants. Preliminary work revealed that participants may use shared devices to access the intervention, which led to STARS being developed on a website as opposed to an app, that would require a log-in each time the intervention is accessed. Additionally, during the guided components of the interventions, participants are asked to indicate a codeword during their onboarding that could be used by the e-helpers to ensure that the person on the other end of the line is those accessing STARS. Furthermore, the chatbot is transparent throughout each lesson that they are a program and not a person. Lastly, e-helpers check digital reports on session use, which include responses to open text fields; responses are analyzed to identify responses that may indicate concern for participants’ well-being and allow for the AE or SAE procedures to be followed. The e-helpers and research staff will be trained in the AE or SAE procedures and subsequent referral pathways prior to the start of the trial.

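### Every active route described for finding adverse events exists only in the STARS arm, so recorded AE and SAE counts should not be read as a between-arm comparison of harms

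*Protocol article*

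**What the plan says.** Under Data Management, Trial Monitoring, and AE Reporting, AEs and SAEs "refer to any undesirable experience of a participant during the trial, whether or not considered related to the trial procedures" or to either intervention, so the definition covers both arms. The same section gives the ways an event enters the record: "All AEs or SAEs reported spontaneously by participants or observed by the research team or e-helpers will be reported to the IFH clinical supervisor". SAEs go to the local ethics review committee (ERC) within 24 hours, and a summary of AEs goes to it every three months. The ERC decides on any action affecting study conduct. There is no data monitoring board.

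The description of STARS gives its participants regular contact. On the guided component: "It consists of 5 weekly telephone calls by trained, nonspecialist e-helpers". On what they type into the chatbot: "Free-text responses will be monitored on a daily basis for any indications that the participant is unsafe". Other Measures adds: "Those randomized into the STARS intervention will complete the Patient Health Questionnaire, 2-item version (PHQ-2) [58] during every other session". Safety Considerations says of this instrument: "The PHQ-2 will be administered in the STARS intervention once a week (every other lesson) and will be monitored by e-helpers". The same section ties the review of open-text fields to event reporting: "responses are analyzed to identify responses that may indicate concern for participants’ well-being and allow for the AE or SAE procedures to be followed".

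The Enhanced Usual Care section describes psychoeducation and a list of services: "This will be delivered through a website where participants register to gain access". No e-helper, call or monitoring is described for that arm. Table 1 lists no AE item at the 8-week (T2) or 20-week (T3) assessment.

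**The concern.** One definition of an adverse event is applied to both arms through two different detection systems. A STARS participant who becomes unwell between baseline and week 8 may tell an e-helper, write it in a monitored field, or show it on the PHQ-2. An EUC participant in the same position has to volunteer it, or happen to disclose it to the research team. Events that occur equally often would then tend to be recorded more often in STARS.

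The error can mislead in two ways. An excess produced by detection could be taken for harm from the chatbot. Conversely, a real excess could be dismissed as a detection artefact, since nothing in the recorded counts separates the two. The readers at stake are those of the final report and the local ERC, if events are shown to them by arm. The Introduction calls this the first randomized trial of the effectiveness of STARS, and the Conclusions tie open release to this trial and a second one, so its harms data are likely to be used.

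**Working it through.** **1. Detection routes side by side, after randomization**

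| Route | STARS | EUC | Source in the protocol article |
|---|---|---|---|
| Spontaneous report | yes | yes | AE Reporting |
| Research team observation | possible | possible | AE Reporting |
| Assessment reminders, up to 3 messages and/or calls | yes | yes | Study Procedures |
| Scheduled e-helper calls | 5 | none described | STARS intervention; Enhanced Usual Care |
| Free-text review | daily | none described | STARS intervention; Safety Considerations |
| PHQ-2 seen by e-helpers | every other session | none | Other Measures; Table 1; Safety Considerations |
| Scheduled AE question | none described | none described | Table 1 |
| HSCL-25 and K10 at weeks 8 and 20 | yes | yes | Study Procedures; Table 1 |

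The routes shared by the arms are passive or incidental as far as AEs are concerned: assessments are self-administered online, and the reminders serve to obtain the questionnaire. The three active routes are in STARS only. With 10 sessions, the PHQ-2 at every other session gives about 10/2 = 5 readings, but only for someone who finishes all sessions.

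**2. What this does to a count**

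Let p be the true risk of an event, and d the probability that an event is recorded. The recorded risk is p × d, so

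recorded RR = true RR × (d in STARS / d in EUC).

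The protocol article states no AE rate and no detection rate, so there is no figure of its own to reproduce and the detection ratio cannot be estimated.

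**3. Illustration, with assumed values**

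Inputs from the document: 344 randomized 1:1, so 344/2 = 172 per arm. Assumed: equal true risk p in both arms, and the detection probabilities shown. Expected recorded cases are 172 × p × d. With a = p × d in STARS, b = p × d in EUC and m = (a + b)/2, the chance of a two-sided 5% test showing a spurious STARS excess is approximately

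Φ{[a − b − 1.96 × √(2m(1 − m)/172)] / √([a(1 − a) + b(1 − b)]/172)}.

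For p = 10%, d = 60% and 40%: a = 0.06, b = 0.04, m = 0.05. The two square roots are 0.02350 and 0.02348, so Φ[(0.02 − 1.96 × 0.02350)/0.02348] = Φ(−1.11) = 13%.

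| True risk, both arms | Detection STARS / EUC | Expected recorded cases | Recorded RR | Chance of spurious excess |
|---|---|---|---|---|
| 10% | 60% / 60% | 10.3 / 10.3 | 1.0 | 2.5% (nominal) |
| 10% | 60% / 40% | 10.3 / 6.9 | 1.5 | 13% |
| 10% | 80% / 40% | 13.8 / 6.9 | 2.0 | 35% |
| 10% | 80% / 20% | 13.8 / 3.4 | 4.0 | 73% |
| 5% | 80% / 40% | 6.9 / 3.4 | 2.0 | 19% |
| 20% | 80% / 40% | 27.5 / 13.8 | 2.0 | 63% |

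The table shows the direction and the mechanism. It does not estimate the bias in this trial. The last column describes what a test would do if someone ran one; the article plans none.

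**The case against.** The strongest case on the other side has five parts.

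- **The research team is a route open to both arms.** This stands. Research staff are trained in the AE procedures and both arms receive reminders. Both also write free text in PSYCHLOPS at weeks 8 and 20, although the article does not say that those fields are screened for safety. Capture in EUC is therefore not nil. But no scheduled AE enquiry by that team is described, so the imbalance remains.
- **Worsening is already measured alike in both arms.** This stands. A reader might infer that harms as a whole cannot be compared, or that deterioration in EUC goes unseen. The document does not support that: the HSCL-25 and K10 are collected identically at weeks 8 and 20. What may be missed in EUC is worsening between assessments, and events that these scales do not measure.
- **No comparative safety claim or between-arm AE test is planned, and the ERC summaries are not said to be split by arm.** This stands, and it makes the point a caution about how counts are read. Any tabulation by arm would still carry the difference in detection.
- **The size is unknown.** This stands. A reader might infer that detection is far higher in STARS, or attach a particular ratio to it. The article gives nothing from which to compute one. It also plans five calls, not a minimum of five, and does not say that a rise in PHQ-2 counts as an AE.
- **The article is condensed, and AE forms may sit in a fuller document.** This stands in part. A common AE question may exist elsewhere, and if so most of the point falls away. The point does not rest on the silence alone, however: the article states the capture rule and assigns each active route to one arm.

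Monitoring STARS users closely is not at issue.

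**Conclusion.** The point holds for recorded AE and SAE counts. Followed as written, the capture rule is likely to ascertain events unequally, with more complete detection in STARS, by an amount that the document does not allow to be sized. Such counts should not be presented as a between-arm comparison of harms, either in the trial report or in the three-monthly ERC summaries. Symptom worsening on the HSCL-25 and K10 at weeks 8 and 20 can be compared, subject to attrition.

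The conclusion rests on two assumptions: that added contact raises the chance of an event being recorded, and that no scheduled AE enquiry common to both arms exists outside the article. It does not bear on the primary efficacy analysis or the sample size.

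**What to change.** 1. Add one identical AE question to the week-8 and week-20 Qualtrics forms of both arms, and base any between-arm statement about AEs on it.
2. Report by arm the proportion with worsening, by a threshold fixed in advance, on the HSCL-25 (change from baseline) and the K10 (change from screening, since Table 1 shows no K10 at baseline). These data are already collected.
3. Tabulate events found by e-helpers or through the chatbot separately, by source.
4. State in the ERC summaries that detection differs by arm.

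Safety monitoring in STARS stays as it is.

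**Cost.** A small amendment, a slightly longer form and extra tables. Participants already past week 8 contribute the question at week 20 only. At the article's status date, 122 days (about 17 weeks) after recruitment began, none of the 228 randomized could have reached week 20. If collection has since ended, items 2 to 4 remain possible and item 1 does not.

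**Limit.** With the assumed 50% attrition, about 172 × 0.5 = 86 per arm would answer at week 20. Loss may differ by arm, so equal questioning reduces the ascertainment bias but does not guarantee its removal.
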